#### Parent Survey

After the student survey was conducted, the children were asked to give an envelope with the parent questionnaire and a return envelope with prepaid postage to their parents. The parents could return the completed questionnaire directly to the KFN by mail. Due to the study design that provides for complete anonymization and therefore no collection of real names, no signature of the participating adults could be obtained. Parents, teachers, and principals decided on their own participation by sending the completed questionnaire to the institute. To match the children’s and the parents’ questionnaires, the children wrote a code on their parents’ questionnaire. This code is only used for matching and does not include any identifiable information. After the matching has been performed, this code will be deleted, rendering the final data completely anonymous. Due to anonymity, parents cannot be reminded to return the questionnaires nor are any incentives offered for participation.

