### Data Analysis

The decision to participate in the Klasse2000 program is made at the school level. Hence, schools self-select for implementing the intervention. This selection bias must be controlled for when comparing the outcomes of children participating in the Klasse2000 and those who did not. The gold standard for preventing selection bias is randomization. There are three major factors that made a randomized trial highly infeasible for this evaluation: (1) as a general intervention, the Klasse2000 targets a high number of outcomes, (2) effect sizes in universal prevention programs can be expected to be rather small, (3) the intervention is implemented during the entire primary school time (ie, over a time span of 4 years). Hence, a very high number of schools would need to be randomized to participate in an intervention over several years. An attractive alternative to an randomized controlled trial is a natural experiment. However, the Klasse2000 is implemented all over Germany, and there are no immediately comparable intervention programs. Hence, neither regional implementation nor the comparison of a comparable program lend themselves for overcoming selection bias. Given these circumstances, a propensity score-matching approach will be implemented as a feasible alternative. The basic idea of a matching approach is as follows: for each student who is currently participating in the Klasse2000 program, a control student will be selected who matches the treatment group participant as closely as possible regarding criteria that are relevant yet unrelated to the participation in the prevention program (ie, gender, socioeconomic status). The matching will be performed with a matching algorithm that assigns weights to each individual in the control group (ie, inverse probability weighting). The estimation of treatment effects will be completed using regression-based analyses that take these weights into account. Simulation studies show that the propensity score-matching approach enables an unbiased estimation of intervention effects [18].

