Prior to analysis, data will be checked for outliers, inconsistencies, and possible transformation. We predict that our sample size will be large enough for our statistical tests to be robust regarding nonnormally distributed variables. Power analyses (ie, a priori) based on a type I error rate (false positive) of α=.05, statistical power of 1−β=.80, and a minimum detectable effect size of ES=0.2 resulted in a required sample size of n=310 (1-tailed) students in each group (intervention and control).

Missing data will be handled using state-of-the-art imputation techniques (multiple imputation in missing non-at-random scenarios [ie, by parametric recursive partitioning] [19,20]). Wherever earlier findings suggest differential effects (ie, regarding gender), subgroup analyses of the above-mentioned hypotheses will be performed. Furthermore, post hoc analyses of different implementation factors potentially contributing to positive treatment effects over time will be conducted.

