### Trial Status Upon Submission of Protocol Revision

During the period this protocol was under revision, data integration was completed. Data integration included linking the child and parent data. Matching was performed with the help of the codes. Figure 2 presents the final number of participants and details on nonparticipation. All 6376 participating children were supplied with a questionnaire for their parents. We received 3324 completed questionnaires which corresponds to a response rate of 52.13%. Of the control group, 52.91% (2119/4005) of parents participated in the survey, whereas 50.82% (1205/2371) of parents of the Klasse2000 group returned the questionnaire. Data analysis is ongoing with only descriptive statistics extracted so far. Beyond the descriptives regarding participation, we analyzed the feedback from the test administrators to confirm data quality. Furthermore, the following demographics were obtained: 50.57% (3140/6352) of the children were female. The average age was 10 (SD 0.62) years. The parent survey was mostly completed by a female parent (2899/3259, 88.95%). The parents completing the survey were on average 42.6 years old. Hypothesis-related results are neither obtained nor published upon resubmission of the protocol to ensure transparent reporting and analyses practices.

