Intervention effects in the following domains are assessed: well-being, health-related behavior, classroom atmosphere, school violence, alcohol and tobacco consumption, and media use. These domains are investigated from the perspective of the students and their parents. Klasse2000 is a large universal prevention program. It is financially supported with donations from well-known institutions such as health care providers and banks and endorsed by experts of national recognition [21]. The program has received the highest possible rating category from the green list prevention provided by the Crime Prevention Council of Lower Saxony. Furthermore, it has received several awards [21]. Given this high status, the results of this study potentially have far-reaching consequences not only for the program at hand but, depending on the nature of results, on other preventions with similar target areas. It is likely that this evaluation will not confirm all hypotheses stated in this protocol. The failure to find and intended intervention effect might be due to a lack of effect or the presence of a meaningful but undetectable effect. Should the intervention fail to produce some of the desired effects, it might warrant improvement. The materials of the Klasse2000 intervention are regularly updated. These updates attempt to improve support for teachers in the implementation, communication with parents, and communication of teaching content to the students. Recent updates include, for example, content for DigiBoards (Digi International) and an interactive website for the students; further digitalization and extension of online health-related content is planned [21]. Depending on the areas that might warrant improvement, successful concepts from eHealth interventions might provide fruitful starting points. Through the wide implementation of the Klasse2000 program, even small effects might be of value from a public health perspective. Future evaluation studies might want to address this issue using assessment tools that assess the targeted health-related behaviors more reliably. Expertise with mobile assessment from the eHealth domain could help future evaluations to quantify small effects.

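### Recursive-partitioning imputation is presented as handling data missing not at random, but as named it assumes missing at random, which matters mainly for the 47.9% of parent questionnaires not returned

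*Protocol article*

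**What the plan says.** The Data Analysis section commits to "multiple imputation in missing non-at-random scenarios [ie, by parametric recursive partitioning" and cites two method sources. The sentence covers missing data in general. Neither it nor the rest of the article mentions a shift parameter, a pattern-mixture or selection model, or a sensitivity analysis for missing data.

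The largest documented gap is in the parent survey. The status section for the protocol revision reports "We received 3324 completed questionnaires which corresponds to a response rate of 52.13" per cent. By group: "Of the control group, 52.91% (2119/4005) of parents participated in the survey", and "50.82% (1205/2371) of parents of the Klasse2000 group returned the questionnaire". Under Parent Survey: "Due to anonymity, parents cannot be reminded to return the questionnaires nor are any incentives offered for participation".

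Parent data belong to the evaluation. The Discussion summary says of the outcome domains: "These domains are investigated from the perspective of the students and their parents". Matching is to use "criteria that are relevant yet unrelated to the participation in the prevention program (ie, gender, socioeconomic status". The article does not say whether socioeconomic status comes from the parent or the student questionnaire.

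**The concern.** The stated mechanism and the stated method do not fit. Recursive partitioning splits cases on variables that were observed and imputes from observed cases, or a model fitted to them, in the same partition. This is valid when, given the observed data, missing and observed values share a distribution, which is the missing-at-random assumption. Partitioning captures interactions and non-linearity among observed variables. It adds nothing about dependence on the value that was not seen.

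This is an error in what the text states, not detail left to an analysis plan. Non-return that depends on family circumstances or on the child's problems is plausible here, and without reminders or incentives it could not be reduced by follow-up. A reader who takes the sentence at face value would think informative non-return had been dealt with. What is at stake is how much can be concluded from the parent-reported results.

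**Working it through.** **1. Reproducing the article's figures.** Inputs are the counts in the status section for the protocol revision.

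- Overall return: 3324/6376 = 52.13%, as stated. Missing: 3052/6376 = 47.9%.
- Klasse2000: 1205/2371 = 50.82%. Missing: 1166/2371 = 49.2%.
- Control: 2119/4005 = 52.91%. Missing: 1886/4005 = 47.1%.
- The groups add up: 1205 + 2119 = 3324 and 2371 + 4005 = 6376.

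**2. What a wrong missing-at-random assumption does to the contrast.** Let m be the missing fraction in a group and d the difference, in SD, between non-returners' true mean and their imputed mean. The true group mean is the imputed group mean plus m × d. The correction to the Klasse2000-minus-control contrast is therefore

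m_T d_T − m_C d_C = 0.492 d_T − 0.471 d_C.

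The shifts are assumptions; the article gives no information on them. The missing fractions are unweighted, and the planned weighting of controls would alter 0.471 somewhat.

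| d_T | d_C | Change in contrast (SD) |
|---|---|---|
| −0.3 | −0.3 | (0.4918 − 0.4709)(−0.3) = −0.006 |
| −0.3 | −0.1 | −0.1476 + 0.0471 = −0.10 |
| −0.1 | −0.3 | −0.0492 + 0.1413 = +0.09 |

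The planned minimum detectable effect is 0.2, so the second row is half of it. For a shift in the Klasse2000 group alone to cancel an effect of 0.2, d_T would have to be about −0.2/0.492 = −0.41 SD.

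**3. Simulation of tree imputation.** Group sizes and return rates are those of the article. Assumed: a true effect of 0.2 SD, a response log-odds slope of 1 per SD, and one student-level predictor correlated 0.3, 0.5 or 0.7 with the parent item. Bootstrap regression trees were fitted within group, with 5 imputations and 40 replicates, without clustering or matching. This is a generic tree method, not necessarily the variant in the cited sources.

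| Mechanism | Complete cases | Tree imputation |
|---|---|---|
| Missing at random, in one group only | 0.33 to 0.49 | 0.21 to 0.22 |
| Not at random, same in both groups | 0.21 to 0.22 | 0.21 to 0.22 |
| Not at random, in one group only | about 0.60 | 0.57 / 0.52 / 0.43 |

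In the last row, the share of the bias removed at correlation 0.3 is (0.599 − 0.566)/(0.599 − 0.197) = 8%. At 0.5 it is (0.604 − 0.517)/(0.604 − 0.200) = 22%. At 0.7 it is (0.608 − 0.434)/(0.608 − 0.204) = 43%. In the middle row the contrast is nearly right, but the control mean stays 0.22 to 0.36 SD too high after imputation (0.39 in complete cases).

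Tree imputation thus does the missing-at-random job well. It leaves most of the bias when non-return depends on the unseen value in one group only.

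**The case against.** The best defence is that this is loose wording in a condensed article. The abbreviation before the method name may have been meant as an example, and the two cited sources, which are not at hand, may describe an extension for data missing not at random. That cannot be excluded. But the text names no such extension, and recursive partitioning offered as an example of handling that mechanism is still mislabelled unless something is added to it.

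Several objections to the reach of the point stand in full:

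- A reader might infer that the imputation gives no protection at all. It does not follow: bias explained by observed data is largely removed, and correlated student data remove part of the rest.
- A reader might apply the 48% to the whole trial. The 6376 are students who took part, and their own reports are not missing because a parent did not reply. That the sentence applies to whole unreturned parent questionnaires is itself an inference, though the text makes no exception.
- A reader might conclude that the propensity score is compromised. That depends on socioeconomic status being parent-supplied, which the article does not state.
- A reader might call the word parametric a mistake. Parametric models can be fitted within the partitions, so the label is unclear but not shown to be wrong.
- The −0.10 SD needs unequal shifts. With equal shifts the contrast hardly moves. The return rates differ by only 2.1 points, which neither shows nor excludes group-specific informative non-return.

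**Conclusion.** The point holds as a mis-stated property of the planned method. As named, imputation by recursive partitioning assumes missing at random, so the claim to cover data missing not at random is unsupported. The consequence is confined mainly to parent-reported outcomes, with 47.9% of questionnaires missing, and extends to matching covariates only if parents supplied them.

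Under the assumed shifts the effect on the contrast runs from about −0.006 SD (equal shifts of −0.3) to about −0.10 SD (−0.3 against −0.1), or +0.09 SD with the groups reversed. These figures show sensitivity; they do not estimate bias. The documents contain no evidence that non-return was in fact informative or differed in kind between groups, and they make no explicit promise to report parent results as robust to it. The student-reported comparisons are not called into question. The correction should be made because it changes what can be claimed from the parent data.

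**What to change.** - **Assumption.** State that the imputation assumes missing at random given the observed student, class and school data, and remove the claim that it handles data missing not at random. If the cited sources do include such a component, name it and its parameters instead.
- **Method name.** Say what is meant by parametric recursive partitioning, including what is fitted within the partitions.
- **Sensitivity analysis.** For parent-reported outcomes, and for any matching covariate supplied by parents, add a delta-adjusted (pattern-mixture) analysis. Use separate shifts for Klasse2000 and control, include the equal-shift case, and report the tipping point at which the conclusion changes. For a covariate, shift its imputed values and re-estimate the propensity score.
- **Source of socioeconomic status.** State which questionnaire supplies it, so that the reach of the problem is clear.

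The cost is a wording change and some extra runs of the same imputation code; no new data are needed. The article reports that no hypothesis-related results had been obtained when the revised protocol was submitted, so at that stage the analysis could still be prespecified.

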### Dissemination

Study results will be disseminated in a final report for the funder (BZgA), who will further disseminate the findings in their own publications. In addition, findings will be submitted to suitable peer-reviewed journals.

## Results

### Trial Status Upon Initial Protocol Submission

Schools were first contacted in March 2017. Between April and June 2017, students and teachers were surveyed. Teachers and principals returned their questionnaires by mail resulting in questionnaires being returned by mail until November 2017. Data entry and cleansing began in May 2018 and was estimated to take until mid-2019.

### Trial Status Upon Submission of Protocol Revision

During the period this protocol was under revision, data integration was completed. Data integration included linking the child and parent data. Matching was performed with the help of the codes. Figure 2 presents the final number of participants and details on nonparticipation. All 6376 participating children were supplied with a questionnaire for their parents. We received 3324 completed questionnaires which corresponds to a response rate of 52.13%. Of the control group, 52.91% (2119/4005) of parents participated in the survey, whereas 50.82% (1205/2371) of parents of the Klasse2000 group returned the questionnaire. Data analysis is ongoing with only descriptive statistics extracted so far. Beyond the descriptives regarding participation, we analyzed the feedback from the test administrators to confirm data quality. Furthermore, the following demographics were obtained: 50.57% (3140/6352) of the children were female. The average age was 10 (SD 0.62) years. The parent survey was mostly completed by a female parent (2899/3259, 88.95%). The parents completing the survey were on average 42.6 years old. Hypothesis-related results are neither obtained nor published upon resubmission of the protocol to ensure transparent reporting and analyses practices.

**Figure 2 figure2:**
[figure not shown]
Sampling procedure, participation, and nonparticipation in the Klasse2000 evaluation study.

## Discussion

### Summary

The aim of the study is a large-scale evaluation of the effectiveness of the Klasse2000 prevention program. The effects of the program as implemented in the field shall be evaluated using a representative sample. As a randomized design was not feasible within the framework of this evaluation, a propensity score-matching approach is used to control for potential selection bias.

Intervention effects in the following domains are assessed: well-being, health-related behavior, classroom atmosphere, school violence, alcohol and tobacco consumption, and media use. These domains are investigated from the perspective of the students and their parents. Klasse2000 is a large universal prevention program. It is financially supported with donations from well-known institutions such as health care providers and banks and endorsed by experts of national recognition [21]. The program has received the highest possible rating category from the green list prevention provided by the Crime Prevention Council of Lower Saxony. Furthermore, it has received several awards [21]. Given this high status, the results of this study potentially have far-reaching consequences not only for the program at hand but, depending on the nature of results, on other preventions with similar target areas. It is likely that this evaluation will not confirm all hypotheses stated in this protocol. The failure to find and intended intervention effect might be due to a lack of effect or the presence of a meaningful but undetectable effect. Should the intervention fail to produce some of the desired effects, it might warrant improvement. The materials of the Klasse2000 intervention are regularly updated. These updates attempt to improve support for teachers in the implementation, communication with parents, and communication of teaching content to the students. Recent updates include, for example, content for DigiBoards (Digi International) and an interactive website for the students; further digitalization and extension of online health-related content is planned [21]. Depending on the areas that might warrant improvement, successful concepts from eHealth interventions might provide fruitful starting points. Through the wide implementation of the Klasse2000 program, even small effects might be of value from a public health perspective. Future evaluation studies might want to address this issue using assessment tools that assess the targeted health-related behaviors more reliably. Expertise with mobile assessment from the eHealth domain could help future evaluations to quantify small effects.

As outlined in the introduction, this evaluation is part of an ongoing evaluation effort of the Klasse2000 intervention. With the timepoint of evaluation in the 4th grade, this evaluation addresses short-term effects. To tentatively quantify medium-term effects, results from a student survey among 9th grade students will be used. The study among 9th grade students did not specifically focus on the target areas but assessed similar domains relating to criminal and health-related behavior. Students from the 9th grade survey indicated whether they had participated in the Klasse2000 prevention program when they attended primary school.

### Limitations

The main limitation of the study is the missing randomization. The main problems of missing randomization are potential selection effects at the school level. Schools that are problem-prone might be more likely to participate in the Klasse2000 program, hoping that participation might reduce prevailing problems. On the other hand, the exact opposite might also be the case. Schools that can be characterized as especially committed and dedicated might decide to participate in the Klasse2000 program. Such selection effects might be counterbalanced with the propensity score-matching approach. It should also be noted that the study design does not include any measurement prior to the intervention. This is a cross-sectional survey that can identify correlations but cannot map causal relationships. The results should be checked within the framework of a longitudinal study design and a preliminary survey and offer necessary space for future research projects.

## Appendix

Multimedia Appendix 1 Chain of effects of Klasse2000.

Multimedia Appendix 2 Schedule of enrollment and assessments.

Multimedia Appendix 3 Standard Protocol Items: Recommendations for Interventional Trials (SPIRIT) checklist.

Multimedia Appendix 4 Ethics approval.

Multimedia Appendix 5 Approval of the state school authority.

Multimedia Appendix 6 Letter to the school principal.

Multimedia Appendix 7 Assessment tools.

Multimedia Appendix 8 Parent information letter.

Multimedia Appendix 9 Grant letter.

## Abbreviations

BZgA: Bundeszentrale für Gesundheitliche Aufklärung (Federal Center for Health Education)
IFT-Nord: Institut für Therapie- und Gesundheitsforschung (Institute for Therapy and Health Research)
KFN: Kriminologisches Forschungsinstitut Niedersachsen (Criminological Research Institute of Lower Saxony)
KiGGS: Studie zur Gesundheit von Kindern und Jugendlichen in Deutschland (Study of the Health of Children and Adolescents in Germany)
SDQ: Strength and Difficulties Questionnaire (German version)
SPIRIT: Standard Protocol Items: Recommendations for Interventional Trials
